## Abstract

**Abstracts:**

**Trial Registration:**

NCT01478009.

## Background

Respiratory viruses are a major cause of influenza-like illness(ILI) symptoms in children and adults, leading to substantial morbidity and mortality each year [1-5]. The complications of ILI symptoms may occur in young children (< 1 year old) and elderly people (> 65 years old), even though ILI symptoms is most often self-limited and restrained to the upper respiratory tract [6-8]. The ILI symptoms is characterized by sudden onset of symptoms such as high fever (> 38°C) and cough in the absence of other diagnosis [9,10]. Other symptoms including myalgia, headache, chills and fatigue can only be used as optional inclusion criteria. Although it is known that rhinovirus infections cause 10% to 40% of the upper respiratory tract infection [11], with coronavirus, parainfluenza virus, adenovirus, echovirus, and coxsackievirus accounting for the remainder of cases [12,13], these viruses produce clinically indistinguishable disease, making specific viral diagnosis difficult [14,15].

Many patients use complementary and alternative medicine (CAM) therapies to treat and prevent the acute respiratory illness in the worldwide. Moreover, few physicians are familiar with their efficacy or safety. Ginseng has been traditionally used in Asia for thousands of years to treat a variety of ailments. The putative active compounds derived from ginseng root processing are the ginsenosides (saponin glycosides), and the water-soluble poly and oligosaccharides [16]. Various studies have shown that both families of compounds can modulate various parameters of the immune response in vitro and in vivo. In clinical trials, healthy subjects that consumed a standardized ginseng extract had a lower incidence of influenza and colds, higher antibody titers, and higher natural killer cell activity [17], as well as increased numbers of total lymphocytes and T helper cells [18]. Ginseng polysaccharide preparations increased cytokine production and mRNA expression by murine macrophages and spleen cells in vitro [19-21].

Currently, the ginseng was well known effect for improving the quality-of-life and immunomodulating effects [21-24]. However, there has been no data on the Korean red ginseng (KRG) accumulated for its preventive activity against ILI onset, as it has shown in American ginseng. The purpose of this study is to evaluate the efficacy of the KRG extract in reducing the frequency, severity and duration of ILI symptoms in healthy adults.

## Methods/Design

### Study objectives

The objectives of this RCT are to study whether the concentrated KRG extract can reduce the frequency, severity, and duration of ILI symptoms in healthy subjects.

#### Primary objective

To evaluate the efficacy of the KRG extract on the frequency of ILI onset in healthy subjects after 12 weeks of consumption.

#### Secondary objectives

To evaluate the following factors in healthy subjects after 12 weeks of consumption on:

A) severity of ILI symptoms

B) duration of ILI symptoms

### Ethics

The study protocol and the written informed consent were approved by the Functional Foods Institutional Review Board of Chonbuk National University Hospital (CUH IRB 2010-02-016). Each subject will be notified regarding the study protocol. Written informed consent will be obtained from each subject.

### Study/trial design

This study is a randomized, double-blind, placebo-controlled, two-armed parallel clinical trial, comparing the KRG extract to placebo. The design of the study will integrate rigorous in accord with principles set out in the Declaration of Helsinki and the Good Clinical Practice guidelines. Our study plan is summarized in Figure 1.

**Figure 1 F1:**
[figure not shown]
**Flow diagram for study**. Summary of the study flow.

### Inclusion criteria for participation in the trial

#### Inclusion criteria

Subjects will be included if they meet the following criteria:

A) Healthy volunteers aged 30 to 70 years

B) Ability to give informed consent

#### Exclusion criteria

The exclusion criteria for the study were:

A) Influenza vaccinated subjects

B) HIV infected and cancer patients

C) Cardiovascular disease, neurologic or psychiatric disease, renal, pulmonary and hepatic abnormalities

D) Upper respiratory infection within two weeks before study

E) History of disease that could interfere with the test products or impede their absorption, such as gastrointestinal disease (Crohn's Disease) or gastrointestinal surgery (a caesum or enterocele surgery are included)

F) Taking medications such as immunosuppressive drugs, corticosteroids, warfarin, phenalzine, pentobarbital, haloperidol, cyclosporine

G) Allergic or hypersensitive to ginseng

H) Laboratory test, medical or psychological conditions deemed by the investigators to interfere with successful participation in the study

I) History of drug or alcohol abuse in prior 2 months

### Recruitment

100 subjects will be recruited through local advertising and doctor referrals from hospital outpatients and general practice clinics. Interested subjects can telephone or email the trial coordinators at the trial conducting sites for further information. Subject information and consent forms will be sent to interested individuals to read over prior to scheduling their first visit.

### Randomization

After enrollment, subjects will be randomly assigned to one of the two groups, either the KRG group or placebo group. The allocation ratio will be 1:1 in blocks of 2. Randomization will be performed at a site remote from trial location. Random numbers will be generated by a computerized random-number generator through the block-randomization method of a software program (Excel, Microsoft Office 2007) for sequence generation. At the time of randomization subjects will draw an envelope. Each envelope contains a number that is concealed to the treatment allocation. Randomization sequence and allocation will be concealed to all study subjects, research staff, investigators and pharmacists until completion of the study. The allocation list will be protected by password access files and held by a non-investigator independent. In the event of an emergency medical situation the individual's randomization code and group allocation can be identify.

### Outcome measures

Subjects will be asked open-ended questions about frequency, severity, and duration of ILI symptoms during telephone follow-ups on days 1, 28, 57, and 85 of treatment and days 35 post-treatment. Subjects will be also asked to report the study nurse immediately (within 24 hours), at the onset of ILI symptoms. Any unfavorable or unintended sign or symptom will be documented.

#### Primary outcome

The primary outcome is the frequency of ILI symptom onset. Subjects will be asked open-ended questions about frequency of ILI onset during study period. The frequency of ILI onset will be checked weekly via telephone.

#### Secondary outcomes

Secondary outcomes will be variety ILI symptoms (including fever, rhinorrhea, nasal congestion, sore throat, cough, sputum, dyspnea, diarrhea, mawkishness, vomiting, headache, and myalgia), severity of ILI symptoms, and duration of ILI symptoms. These outcomes will be checked weekly via telephone. The schedule of assessments is presented in Table 1.

**Table 1 T1:** A brief study schedule at every visit.

	*Screening* *Visit 1*	*Baseline* *Visit 2*	*Visit 3*	*Visit 4*	*Visit 5*	*Follow up* *(Visit 6)*
	
	*D-21* *~D-1*	*Week 0* *D0*	*Week 4* *D28*	*Week 8* *D56*	*Week 12* *D84*	*Week 17* *D119*
***Informed consent form ***	◯					

***Demographic information taking^1 ^***	◯					

***Medical history taking ***	◯	◯	◯	◯	◯	

***Inclusion/exclusion criteria check ***	◯	◯				

***Physician examination^2 ^***	◯				◯	

***Vital sign measurement ***	◯	◯	◯	◯	◯	

***Concomitant drugs check ***	◯	◯	◯	◯	◯	

***Electrocardiogram(ECG) ***	◯				◯	

***Questionnaires for symptoms related to ILI^3^***	◯	◯	◯	◯	◯	◯

***Laboratory test^4 ^***	◯				◯	

***Study product distribution ***		◯	◯	◯		

***Compliance checking ***			◯	◯	◯	

***Adverse event monitoring ***			◯	◯	◯	◯

^◯ ^*: Item need to be performed during the visit*

^1 ^Sex, date of birth, age, contact address and phone number

^2 ^Include present illness, past history taking

^3 ^Frequency of ILI symptom onset, severity of ILI symptoms, and duration of ILI symptoms

^4 ^Blood test (WBC, RBC, hemoglobin, hematocrit, platelets count, AST, ALT, ALP, gamma-GTP, albumin, BUN, creatinine, glucose, total bilirubin, total protein), urine test (specific gravity, pH, protein, ketone, glucose, bilirubin, urobilinogen, nitrite, microscopic (RBC, WBC))

#### ILI assessments

Subjects will be asked to record if they experienced any of the following 8 symptoms: sore throat, runny nose, nasal congestion, sneezing, hoarseness, myalgia, earaches, fever, headache, and cough (Table 2). In this self-assessment, subjects will be recorded the number of days they experienced each symptom. Subjects will be contacted by telephone each week to report the ILI symptoms and to assure compliance to the study protocol. They will be also asked to record if the study medication helped in shortening duration of their symptoms, and to list any additional medications taken for the symptoms. Subjects will be recorded daily symptom severity in a journal using a 4-point severity score index (0 = no symptom, 1 = mild symptom, 2 = moderate symptom and 3 = severe symptom).

**Table 2 T2:** Questionnaire for Influenza-Like Illness

Symptoms	Score	Duration (days)	nonattendance (days)
Sore throat	**□**0 **□**1 **□**2 **□**3		
Runny nose	**□**0 **□**1 **□**2 **□**3		
Nasal congestion	**□**0 **□**1 **□**2 **□**3		
Sneezing	**□**0 **□**1 **□**2 **□**3		
Hoarseness	**□**0 **□**1 **□**2 **□**3		
Myalgia	**□**0 **□**1 **□**2 **□**3		
Earaches	**□**0 **□**1 **□**2 **□**3		
Fever	**□**0 **□**1 **□**2 **□**3		
Headache	**□**0 **□**1 **□**2 **□**3		
Cough	**□**0 **□**1 **□**2 **□**3		
Total score			

0: None symptoms 1: Mild symptoms

2: Moderate symptoms 3: Severe symptoms

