#### Adverse events and monitoring safety

All unexpected adverse events related to KRG intake will be reported to the investigator by subjects and write on the individual case report form by the investigator. Safety will be assessed by the reporting of clinical laboratory tests, vital sign measurements, and adverse events. Clinical laboratory tests, including AST/ALT, BUN/creatinine, red blood cell (RBC) count, white blood cell (WBC) count, hemoglobin, hematocrit, number of platelets, and number of differentiated cells will be determined at weeks 0 (baseline) and 12 (end of the trial). Vital signs of each subject will be checked with monitoring of adverse events (nausea/vomiting, fatigue, allergic reaction, and any adverse events related to KRG extract intake) after each visit.

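### The weekly calls are described for ILI and compliance while scheduled adverse event enquiry is tied to visits 28 to 35 days apart, so mild, brief adverse events may be under-recorded

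*Protocol article*

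**What the plan says.** **Weekly contact.** Under Primary outcome: "The frequency of ILI onset will be checked weekly via telephone". Secondary outcomes says the same of the ILI symptoms, their severity and their duration. ILI assessments gives the purpose of the call: "Subjects will be contacted by telephone each week to report the ILI symptoms and to assure compliance to the study protocol". None of the three sections names adverse events as a topic.

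**Scheduled safety enquiry.** In Table 1 the row "Adverse event monitoring" is marked at Visits 3, 4, 5 and 6, that is D28, D56, D84 and D119. Adverse events and monitoring safety names nausea/vomiting, fatigue, allergic reaction and "any adverse events related to KRG extract intake) after each visit".

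**Other routes.** The same safety section states: "All unexpected adverse events related to KRG intake will be reported to the investigator by subjects", and the investigator enters them on the case report form. Outcome measures lists "telephone follow-ups on days 1, 28, 57, and 85 of treatment and days 35 post-treatment", asks for ILI onset to be reported to the study nurse within 24 hours, and adds: "Any unfavorable or unintended sign or symptom will be documented".

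**Use of the data.** Statistical analysis compares the proportions of subjects with adverse events between arms by Pearson chi-square or Fisher's exact test. Sample size gives 100 participants, 50 per arm.

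**The concern.** The same subjects are asked about efficacy every 7 days and, on the stated schedule, about safety every 28 to 35 days. Recall of a mild event that lasted a day or two is likely to be poorer after four or five weeks than after one. That is general experience with recall; the article gives no figure for it.

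Two features of the article make this more than a matter of taste.

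- **Overlapping symptoms.** Secondary outcomes includes vomiting among the ILI symptoms checked weekly. The safety section lists vomiting among the adverse events monitored at visits. One episode can thus be asked about as an efficacy event within a week and as a safety event up to four weeks later.
- **A narrow route between visits.** Reporting by subjects in the safety section is worded for events that are both unexpected and related to KRG. Read literally, it leaves out expected events and asks a blinded subject to judge relatedness. It has no time limit, whereas ILI onset has one of 24 hours.

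At stake are the completeness of the adverse event record and the sensitivity of the planned comparison in a small trial.

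**Working it through.** The plan gives no figure of its own to reproduce here. The checks are interval arithmetic, a comparison of symptom lists, and one illustration with assumed rates.

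**1. Intervals between scheduled adverse event enquiries** (Table 1, from D0):
- 28 − 0 = 28; 56 − 28 = 28; 84 − 56 = 28; 119 − 84 = 35 days.
- The contact days in Outcome measures (1, 28, 57, 85, then 35 days later) give 27, 29, 28 and 35 days.
- Against a 7-day call: 28/7 = 4 times longer on treatment, 35/7 = 5 times longer in follow-up.

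**2. Number of scheduled enquiries**
- D0 to D84: 3 in Table 1, against 84/7 = 12 weekly calls.
- D0 to D119: 4 in Table 1, against up to 119/7 = 17 calls if they continue through follow-up, which the article does not state.

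**3. Mean lag from onset to the next scheduled enquiry**, assuming onset uniform over D0 to D119:
- Sum of (interval²/2) divided by 119 = (3 × 28² + 35²)/(2 × 119) = 3577/238 = 15.0 days.
- With weekly enquiry throughout: 7/2 = 3.5 days.

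**4. Symptom lists side by side**

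| Named adverse event (safety section) | In the weekly ILI list (Secondary outcomes) | In Table 2 |
|---|---|---|
| Vomiting | yes | no |
| Fatigue | no | no |
| Allergic reaction | no | no |

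Vomiting falls within the stated weekly enquiry, but as an ILI symptom. Fatigue and allergic reaction are not named as weekly topics.

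**5. What equal under-recording does to the comparison.** Let a share c of subjects with an event be recorded in each arm, with no false reports. The recorded proportions are c·p1 and c·p2.
- Absolute difference: c(p1 − p2), which shrinks by the factor c.
- Risk ratio: c·p1/(c·p2) = p1/p2, which is unchanged.

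Illustration with assumed true proportions of 30% and 10% (not in the article), 50 per arm, two-sided 5%, Pearson chi-square throughout, power by exact enumeration:

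| c | Recorded proportions | Difference | Risk ratio | Power |
|---|---|---|---|---|
| 1.00 | 30% vs 10% | 20 points | 3 | 73% |
| 0.75 | 22.5% vs 7.5% | 15 points | 3 | 59% |
| 0.50 | 15% vs 5% | 10 points | 3 | 39% |

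The values of c are assumptions too. The table shows the direction and form of the effect, not the loss to expect in this trial.

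**The case against.** The strongest case against is that the article does not say adverse events go unasked in the weekly calls.

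- **Table 1 lists visit items only.** It also marks the ILI questionnaire and compliance at visits only, although the text covers both weekly. A missing weekly mark for adverse events therefore proves nothing about the calls. This stands as far as Table 1 goes. The text, however, assigns the weekly call to ILI and compliance and places adverse event monitoring at visits, so the article states a method and is not merely silent.
- **Other routes exist.** A visit enquiry can cover the whole period since the last visit, subjects report some events themselves, and Outcome measures wants any unfavourable sign documented, without limiting this to visits. This stands too. But the self-report route is narrow, and the Outcome measures sentence says what is documented, not when subjects are asked.
- **The article is condensed.** A call script may sit in the full protocol. That is fair, and it is a reason for low priority.

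A reader might infer that adverse events are asked about only every 28 to 35 days and that transient ones are lost. The routes above do not support either word. A reader might also infer that the safety comparison is simply biased toward no difference. With equal capture in both blinded arms that is true of the absolute difference but need not be true of the risk ratio. Finally, 12 calls against 3 enquiries counts contacts, not missed events; the article gives no recall rate and no time of onset for these events.

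**Conclusion.** The point holds as a low-cost improvement, not as an error: no figure is wrong. Scheduled adverse event enquiry is 28 days apart on treatment and 35 days apart in follow-up, beside a 7-day call described for ILI and compliance. Mild, brief events between visits may be under-recorded, and vomiting may be counted as an ILI symptom without reaching the adverse event record.

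The extent cannot be estimated from the article. If capture is incomplete and equal in both arms, the recorded rates, the absolute difference and the power of the comparison fall. The conclusion rests on reading the stated purpose of the weekly call as its actual content; if the full protocol already includes an adverse event question in the call, only the wording needs to change. Priority: minor.

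**What to change.** - Add one non-leading adverse event question to the existing weekly call, in both arms, from week 1, and record the onset date of anything reported.
- State this under ILI assessments, where the call is described, and under Adverse events and monitoring safety.
- Use the scheduled visits to review the weekly entries, including whether a gastrointestinal symptom reported as ILI also belongs in the adverse event record.

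The longest scheduled gap on treatment falls from 28 to 7 days, and scheduled enquiries over D0 to D84 rise from 3 to up to 12. No new contact or staff is needed. The cost is one more question per call and slightly more adverse event entries to process.

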### Statistical analysis

#### Baseline data and Outcomes data

The effects of KRG extract or placebo treatment on the frequency, severity, and duration of symptoms related to ILI prior to the onset of influenza season will be analyzed. The Pearson chi-square test or Fisher's exact test (if the minimum expected count will be less than 2 or the ratio of expected counts lower than 5 will be more than 20%) will be used to compare the proportions of subjects reporting symptoms related to ILI and adverse events. The data will be analyzed for all of the subjects who had been randomly assigned to a group, excluding those who provided only baseline information. An intention-to-treat and per-protocol analysis will be performed.

For the subset of subjects who reported ILI-related symptoms, the total score of severity and the duration for which symptoms will be reported and the two groups will be compared using Mann Whitney U test between two groups. A value of p < 0.05 will be considered statistically significant.

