#### Compliance

The KRG soft capsules remaining after each visit will be quantified in order to enhance medication compliance. Subjects whose compliance with the KRG extract capsules is ≤ 70% of the total dose will be considered to have dropped-out.

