#### Sample size

This pilot study is the first clinical trials using KRG extract for Korean population. So, there was limited information about the prevention of influenza incidence or symptom releases. Therefore, we had designed a preliminary test using total 100 participants (50:50).

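### The only stated between-arm comparison of adverse events is a p < 0.05 test, which at 50 per arm has little power for uncommon events; a risk difference with its 95% CI should be the main safety summary

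*Protocol article*

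**What the plan says.** Under Baseline data and Outcomes data, the Protocol article names the Pearson chi-square test, with Fisher's exact test as the fallback "if the minimum expected count will be less than 2 or the ratio of expected counts lower than 5 will be more than 20" percent. One sentence covers efficacy and safety together: these tests "will be used to compare the proportions of subjects reporting symptoms related to ILI and adverse events". The criterion is "A value of p < 0.05 will be considered statistically significant". No interval, bound or margin is attached to the adverse event comparison.

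Under Adverse events and monitoring safety, the article adds that "Safety will be assessed by the reporting of clinical laboratory tests, vital sign measurements, and adverse events". That section gives no further comparison between arms.

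Under Sample size, the trial is called a pilot with limited prior information, and the number is fixed without an event rate, effect or power: "we had designed a preliminary test using total 100 participants (50:50"). The Discussion leaves confirmatory conclusions on efficacy and safety to a full-scale trial.

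**The concern.** Testing for a difference at p < 0.05 is a reasonable way to look for a benefit, because a non-significant result there is simply inconclusive. For harm, the same output is easily read as reassurance. Whether that reading would be justified depends on how often the test would miss a relevant excess, and on whether the report shows the range of excess that the data leave open.

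The subjects are healthy volunteers taking the product for prevention, so a moderate excess of adverse events would matter. With 50 per arm and uncommon events, the planned comparison could often end in a non-significant p-value although an excess exists. The p-value alone would not tell the reader how large an excess had been ruled out.

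**Working it through.** **Inputs from the Protocol article**
- 50 subjects per arm (Sample size), allocated 1:1 (Randomization).
- Chi-square test, or Fisher under the stated expected-count rule; p < 0.05 (Baseline data and Outcomes data).

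**Assumptions**
- The test is two-sided; the article does not say.
- The article gives no adverse event rate, so a range is shown.
- The article states no dropout rate, so 45 and 40 evaluable per arm are used as a sensitivity check.

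There is no planned power figure to reproduce.

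**Step 1: the rule at 50 vs 50.** With t events in total, the expected counts are t/2, t/2, 50 - t/2 and 50 - t/2. If t < 10, two of the four cells (50%, above the 20% limit) fall below 5 and Fisher applies. For uncommon events the rule therefore uses the more conservative test.

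**Step 2: miss rate.** For true rates p1 (KRG) and p0 (placebo), all 51 x 51 outcome pairs (a, b) are enumerated:

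miss = 1 - Σ Bin(a; 50, p1) × Bin(b; 50, p0) × 1[p-value(a, b) < 0.05]

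The p-value is taken from whichever test the plan's rule selects.

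| Placebo vs KRG | Ratio | Missed, 50 per arm | Missed, 45 per arm |
|---|---|---|---|
| 2% vs 4% | 2 | 99% | 99.6% |
| 5% vs 10% | 2 | 91% | 93% |
| 10% vs 20% | 2 | 70% | 73% |
| 20% vs 40% | 2 | 40% | 44% |
| 2% vs 6% | 3 | 97% | 98% |
| 5% vs 15% | 3 | 65% | 71% |
| 10% vs 30% | 3 | 27% | 31% |
| 20% vs 60% | 3 | 1% | 2% |

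**Step 3: where a miss stops being the likelier outcome.** At 50 per arm, a doubling is missed 52.7% of the time at a placebo rate of 16% and 49.6% at 17%. A tripling is missed 54.2% of the time at 6% and 49.5% at 6.5%. The crossovers are therefore about 17% and 6.5%. At 40 per arm they rise to about 20% and 8%.

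**Step 4: what a non-significant result can hide.** Take 9/50 on KRG and 3/50 on placebo, a constructed example. The expected counts are 6, 6, 44 and 44, so chi-square applies:

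X² = 100 × (9×47 - 3×41)² / (50 × 50 × 12 × 88) = 100 × 300² / 2,640,000 = 3.41, p = 0.065.

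The Newcombe interval combines the two Wilson intervals, 9.8% to 30.8% for 18% and 2.1% to 16.2% for 6%. The difference is 12 points.
- Lower limit: 12 - √[(18 - 9.8)² + (16.2 - 6)²] = -1 point.
- Upper limit: 12 + √[(30.8 - 18)² + (6 - 2.1)²] = +25 points.

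By the same method, 5/50 vs 3/50 gives -8 to +16 points and 10/50 vs 4/50 gives -2 to +26 points. Both are non-significant under the plan's rule.

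**The case against.** The strongest reply is that this is a pilot that claims no more than it can deliver. Safety is not among the stated objectives. The article never says that a non-significant difference will be taken as safe, and it leaves the confirmatory safety conclusion to a larger trial. Low power for adverse events is inherent in 100 subjects, and an interval does not change that. Interval estimates are also commonly left to an analysis plan, which is not shown. All of this stands, and it means that the absence of an interval is not in itself an error.

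Three stronger readings are tempting, and the documents do not support them.
- A reader might infer that a doubling or tripling of adverse events would usually be missed, whatever the rate. That depends on a placebo rate the article does not give. A miss is the likelier result for a doubling only below about 17%, and for a tripling only below about 6.5%.
- A reader might infer that safety is judged by this test alone. The article also reports laboratory tests, vital signs and adverse events descriptively. The test is the only between-arm comparison stated, which is a narrower point.
- A reader might infer that the plan treats non-significance as proof of safety. No section says so.

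What remains is that the article does state how adverse events will be compared. The method it names gives less information at this sample size than an estimate with its interval.

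**Conclusion.** The point holds as a modest improvement to a stated analysis. With 50 per arm and assumed placebo rates of 5% to 10%, the planned test misses a doubling of adverse events 91% to 70% of the time. It misses a tripling from 5% in 65% of trials. For commoner events it performs better, as 20% vs 40% (missed 40%) and 10% vs 30% (missed 27%) show. The size of the problem therefore rests on the unknown event rate, on a two-sided test and on nearly all subjects being evaluable; with fewer evaluable subjects the miss rates rise. A non-significant p-value from this test should not be read as evidence of safety, and on its own it would not show the excess that remains possible.

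**What to change.** In Baseline data and Outcomes data, state that adverse events will be reported by arm as the number and percentage of subjects, and that the main between-arm safety summary will be the KRG minus placebo risk difference with its 95% confidence interval (for example Newcombe). Add that any chi-square or Fisher p-value is supplementary and that a non-significant result will not be taken as evidence of safety. The test need not be removed.

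The cost is one or two sentences, with no extra subjects or data. The downside is that the intervals will be wide, with upper limits of about 16 to 26 percentage points in the three examples above, so the safety statement will look less favourable. The change does not raise the power of the trial; it shows what 50 per arm can and cannot exclude.

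### The ITT comparison of crude ILI proportions takes no account of time observed, so subjects who leave early without a reported ILI contribute as non-events

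*Protocol article*

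**What the plan says.** Under Primary outcome, the protocol article states: "The primary outcome is the frequency of ILI symptom onset". It adds: "The frequency of ILI onset will be checked weekly via telephone". The Primary objective sets the time frame at 12 weeks of consumption.

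Under Baseline data and Outcomes data, the Pearson chi-square test or, with small expected counts, Fisher's exact test "will be used to compare the proportions of subjects reporting symptoms related to ILI and adverse events". No other stated test can serve the frequency outcome, because the Mann-Whitney test is kept for severity and duration among subjects with symptoms. The analysis set is "all of the subjects who had been randomly assigned to a group, excluding those who provided only baseline information". The same section says: "An intention-to-treat and per-protocol analysis will be performed".

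Under Compliance, subjects who take 70% or less of the total dose are treated as drop-outs. The article does not say how this affects either analysis set.

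**The concern.** The stated test and the stated set have to be read together. The set admits anyone who gave any information after baseline, however little. The test asks only whether a subject reported ILI symptoms. A subject who answers one weekly call, reports nothing and then leaves meets the set definition and has reported no ILI. That subject stays in the denominator as a non-event, although most of the 12 weeks went unobserved.

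Two harms follow. If the arms lose subjects at different rates, the arm that loses more shows a lower ILI proportion for that reason alone. If they lose subjects equally, both proportions shrink, the difference between them shrinks too, and power falls.

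There is also a mismatch with the outcome's name. A proportion of subjects is an ever/never measure, so a second onset in the same subject does not count.

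**Working it through.** **From the protocol article:** 50 subjects per arm (Sample size), a 12-week window (Primary objective), and a significance threshold of 0.05 (Baseline data and Outcomes data; taken as two-sided). The article derives the sample size from no event rate, effect size or power, so there is no stated figure to reproduce.

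**Assumed, because the article gives no values:** true 12-week risk r of 20% to 50%; constant ILI hazard; drop-out unrelated to ILI; drop-out proportion d of 10% in one arm and 30% in the other; no treatment effect. Leavers go either uniformly over the 12 weeks or all at week 2.

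**Formula.** Weekly hazard h = -ln(1 - r)/12. The expected crude proportion is

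(1 - d) × r + d × q,

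where q is the chance that a leaver has ILI before leaving:
- uniform leaving: q = 1 - r/(12h)
- all leaving at week 2: q = 1 - exp(-2h)

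**Worked case, r = 40%.** 12h = -ln(0.6) = 0.5108.
- Uniform: q = 1 - 0.4/0.5108 = 0.217. With d = 10%: 0.9 × 0.4 + 0.1 × 0.217 = 38.2%. With d = 30%: 0.7 × 0.4 + 0.3 × 0.217 = 34.5%. Spurious difference 3.7 points.
- Week 2: q = 1 - exp(-0.5108/6) = 0.0816. With d = 10%: 36.8%. With d = 30%: 30.4%. Spurious difference 6.4 points.

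**Range over risk.** Type I error is by exact binomial enumeration of the Pearson test at 50 per arm.

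| True risk | Uniform: difference (points) | Uniform: type I error | Week 2: difference (points) | Week 2: type I error |
|---|---|---|---|---|
| 20% | 1.9 | 0.061 | 3.3 | 0.077 |
| 30% | 2.8 | 0.062 | 4.8 | 0.087 |
| 40% | 3.7 | 0.067 | 6.4 | 0.102 |
| 50% | 4.4 | 0.080 | 7.8 | 0.131 |

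Without drop-out the same test rejects in 0.050 to 0.057 of trials.

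**Equal drop-out, true effect.** With true risks of 50% versus 25% and uniform leaving, power is 74.5% with no drop-out, 71.5% at 10%, 68.5% at 20% and 65.6% at 30% in both arms. At 30% the expected proportions are 43.4% and 21.4%, so the 25-point effect appears as 21.9 points (unrounded). Under no effect, equal drop-out leaves the type I error about nominal.

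**Repeat episodes.** If episodes follow a Poisson process (an assumption), the share that are repeats is 1 - r/(12h): about 10%, 16%, 22% and 28% at risks of 20%, 30%, 40% and 50%. An ever/never measure drops these.

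**The case against.** - **Scoring leavers as ILI-free is not a stated rule.** That is right. A reader might infer that the article prescribes it, but it only follows from the stated set and the stated test, and only for leavers with no reported ILI. An analysis plan that is not shown could add censoring or imputation. The article does fix the test and the set, however, and neither allows for time observed.
- **A per-protocol analysis is also planned.** A subject who leaves at week 2 has taken at most 2/12 = 17% of the dose, so a per-protocol set that excludes drop-outs would probably leave that subject out. This does not change the ITT set.
- **Frequency may mean incidence.** The Discussion speaks several times of ILI incidence, and the proportion affected over a fixed period is a standard incidence measure. A reader might infer that the test is simply wrong for the outcome. The article does not support that, because the wording is open to both readings. The time-at-risk point holds under either.
- **Repeat episodes do not argue for a log-rank test.** Time to first onset ignores them just as chi-square does. They justify only an added count analysis.
- **Onset dates may not be on record.** Table 2 has fields for score, duration and nonattendance but none for onset date. Timing would have to come from the weekly calls, the 24-hour onset reports and the daily journal.
- **The bias is small against the noise.** At 40% risk and 50 per arm, the standard error of the difference is √(2 × 0.4 × 0.6/50) = 9.8 points, so 3.7 points is under 0.4 standard errors. Nothing in the article predicts unequal drop-out.
- **A reader might infer that only p-values will be reported.** The article sets a threshold and does not rule out estimates, and a condensed article may leave out such detail.

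**Conclusion.** The point holds for the ITT analysis as written: comparing crude proportions in a set with no minimum follow-up treats unobserved time as ILI-free time for subjects who leave without a reported ILI.

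Under the assumed 10% versus 30% drop-out and no effect, the spurious benefit is 1.9 to 4.4 points with uniform leaving (type I error about 0.06 to 0.08) and 3.3 to 7.8 points if all leave at week 2 (about 0.08 to 0.13). Week 2 leaving is an unfavourable case. A bias in favour of one arm requires unequal drop-out; equal drop-out costs power and understates the effect. The article does not support the stronger conclusion that a bias towards KRG is to be expected. The change is worth making because it is cheap, not because the planned test is invalid.

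**What to change.** In Baseline data and Outcomes data, make the analysis of the primary outcome time to first ILI onset within the 12-week window of the Primary objective, censored at last contact or at D84, whichever comes first. Use a log-rank test, with a Kaplan-Meier risk difference and its 95% confidence interval at D84. State that onset is taken from the weekly calls, the 24-hour reports and the daily journal. Keep chi-square or Fisher as a sensitivity analysis.

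Say whether frequency means subjects with at least one onset or the number of onsets. As a supportive analysis, add episodes per person-week by Poisson or negative binomial regression with log follow-up time as offset, since neither chi-square nor the log-rank test on first onset counts repeats.

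The cost is revised wording, a little programming and care in deriving onset dates and last contact. The limitation is that censoring still assumes drop-out is unrelated to ILI risk, which is milder than treating leavers as free of ILI to week 12.
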